#### **4.3 Phase II: Implementation and Evaluation (objective 2-3), 12 months implementation:**

We will conduct a parallel two-arm, cluster randomized controlled trial of the enhanced NCD-COVID-19 integrated care package in rural Punjab, Pakistan. The Province of Punjab has 110 million inhabitants in 36 districts; about two-third of the population live in rural areas. The rural population is served mainly by a network of more than 315 rural health centers (RHCs), and 120 (sub)district level hospitals. Each rural health centre provides primary care to a catchment population of 200,000 rural inhabitants. The staff of RHC includes: 1) three or more doctors; 2) five or more allied health workers including paramedics, lady health visitors, nurses, dispenser, laboratory technician; and 3) support staff. RHCs offer diagnostic and treatment services for communicable diseases, obstetric and neonatal care, child health, malnutrition and NCDs. The Directorate General Health Services Punjab has already scaled integrated diabetes-hypertension care at the district hospital level, including diagnosis, treatment, lifestyle counselling and reporting tools – using a package of care developed with ASD and Leeds. Currently, ASD is leading the WDF project in 75 RHCs among 10 districts in Punjab to offer NCD care which is focused on diabetes-hypertension diagnosis and treatment.

**4.3.1 Randomization and blinding:** We will recruit and randomize 30 out of the 75 RHCs which currently offer hypertension-diabetes care. RHCs, stratified by district, will be randomly allocated into

intervention and control at 1:1 ratio. RHCs will not be blinded due to the nature of the intervention. To mitigate the risk of bias, we will: 1) mask the statistician and the Data Safety Monitoring Board (DSMB) when data is presented and analyzed; and 2) employ objective outcomes.

**4.3.2 Inclusion and exclusion criteria:** We will invite all clinically diagnosed persons living with hypertension (SBP > 140 mmHg or DBP > 90 mmHg) who 1) reside in the selected RHCs, 2) are 25 years or older, 3) and provide informed consent, and 4) have a smartphone or can access to a smartphone from a relative..

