#### **4.6 Data collection, management, and analysis**

We will collect patients' demographic and social information, their exact home address, blood pressures, body weight, and height, knowledge, attitude and practice (KAP) regarding NCD and COVID at the randomization and Month 10 in the RHCs. The RHC doctor will measure the participants' blood pressure using a calibrated electronic blood pressure apparatus after 5 minutes of seated rest, and measure body weight and height. Participants will be asked to provide a blood sample in the RHC at the recruitment and Month 10. In addition, we will also collect patient blood pressures in Month 10 using same methods. Blood samples will be collected and analyzed in RHC according to national guidelines for fasting blood glucose. We will collect attendance rates using the routine patient treatment cards in RHCs to record both physical and virtual consultations. We will conduct a survey at the recruitment to collect patient demographics, socioeconomics, smoking status, COVID-19 immunization status, health service use, medial, KAPs for NCD and COVID, and health care and related costs. The survey will be repeated at Month 10 in the last follow-up to collection information regarding COVID-19 symptoms and related health care consultation and use. Any deaths that occur in patient group during this period will be assigned a probable cause, as determined by a method called verbal autopsy.

Overall, we will conduct mixed methods evaluation to examine the utility of the NCD-COVID guideline, the platforms and care process to inform acceptability, feasibility, reach, adoption, and implementation related challenges (in Section 5.2).

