We will present appropriate descriptive statistics for RHCs and individual level, along with appropriate summary statistics and their associated 95% confidence intervals for all the outcomes. Then, for all outcomes, we will produce a main set of estimates of intervention effectiveness using cluster-level methods of analysis suitable for cluster trials. In particular, a linear mixed effect model will be used to analyse the primary outcome (systolic blood pressure) adjusting for the baseline systolic blood pressure. For other continuous secondary outcomes a similar analysis will be employed. Binary secondary outcomes will be analysed with the generalized estimating equation (GEE) approach, employing a binomial family with logit link function and exchangeable working correlation structure on sites. There will no interim analyses. Intent to treat analysis will be conducted.

**4.4 Phase III: Evaluation and Knowledge Dissemination (Objective 3&4) (3 months):** The phase III will also be used to complete the outcome evaluation, process and cost-effective evaluations highlighted in phase II. We will work together to 1) compile and analyze quantitative and qualitative data in Pakistan and Canada and produce reports and papers; and 2) coordinate with Department of Health Services at the provincial and national levels to translate evidence into program decisions for providing integrated COVID-NCD care in Pakistan and other LMICs. In addition, we will conduct four activities regarding the success factors for scaling up our interventions in LMICs: 1) budget impact analysis: we will review the project costs, and estimate the annual costs for implementation which will inform the affordability in the health system; 2) develop a practical monitoring framework with multi-stakeholders, to inform its usability for future scale-up to other countries; 3) document factors that either facilitate or hinder scale-ups; and 4) provide detailed scale-up plans. The results of the implementation and scale-up will be communicated to policy makers by constantly engaging them in all the stages of the study using workshops, meetings and policy briefs. We will publish the results in leading academic journals and provide policy briefs to policymakers.

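### Rural health centres are randomised within districts, but the planned outcome models leave district out, so the primary confidence interval is probably too wide

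*Protocol*

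**What the plan says.** Section 4.3.1 describes the allocation: "We will recruit and randomize 30 out of the 75 RHCs which currently offer hypertension-diabetes care". It continues: "RHCs, stratified by district, will be randomly allocated into" two arms, with "intervention and control at 1:1 ratio". The pool of centres is described in section 4.3: "ASD is leading the WDF project in 75 RHCs among 10 districts in Punjab". The protocol does not say how many of the ten districts will supply the 30 trial RHCs.

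The models are in section 4.6. For the primary outcome, "a linear mixed effect model will be used to analyse the primary outcome (systolic blood pressure) adjusting for the baseline systolic blood pressure". Then: "For other continuous secondary outcomes a similar analysis will be employed". Binary secondary outcomes are to be analysed with the "generalized estimating equation (GEE) approach, employing a binomial family with logit link function and exchangeable working correlation structure on sites". District appears in none of these sentences, and the GEE sentence names no covariate at all.

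Baseline values exist for at least two binary outcomes. Blood pressure is measured at the start (sections 4.3.5 and 4.6), and the recruitment survey listed in section 4.6 includes "smoking status, COVID-19 immunization status, health service use".

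**The concern.** Stratifying by district balances the arms within each district, so differences between districts largely cancel out of the treatment contrast. A model without district does not know this. It treats district differences as ordinary variation between RHCs and leaves them in the standard error. The reported interval is then wider than the design warrants.

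In a non-inferiority trial with a 2.5 mmHg margin, what is at stake is a false failure: the intervention may be no worse, yet the upper confidence limit crosses the margin because the standard error is inflated.

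This is more than a detail left to a statistical analysis plan. The protocol names the adjustment set for the primary model, and that set omits the factor on which its own randomisation rests.

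**Working it through.** **Inputs from section 4.3.6.** Margin 2.5 mmHg, SD 11 mmHg, one-sided 5%, power 90%, ICC 0.03, 40 patients per RHC, 15 RHCs per arm.

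**Assumptions.** f is the share of between-RHC variance that lies between districts; 0, 25, 50 and 75% were tried. Two layouts were tried: five districts of six RHCs, and ten districts of three. The true difference is zero for power. There is no baseline adjustment.

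**The plan's own figures.** Individually randomised: n = 2 × (1.645 + 1.282)² × 121 / 2.5² ≈ 332 per group, which agrees with the protocol. The stated clustered figure of 614 is not reproduced: 332 × (1 + 39 × 0.03) = 332 × 2.17 ≈ 720. At the stated inputs, 15 RHCs of 40 per arm give about 83% power (t, 28 df) or 85% (normal). That discrepancy is a separate matter. It is noted here because it sets the starting power below.

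**Standard error if district does not matter (f = 0).**
- Between-RHC variance: 0.03 × 121 = 3.63.
- Variance of an RHC mean: 3.63 + 0.97 × 121 / 40 = 3.63 + 2.934 = 6.564.
- SE of the difference: √(2 × 6.564 / 15) = 0.936 mmHg.

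**True standard error at f = 50%.** District variance is 0.5 × 3.63 = 1.815, leaving 6.564 − 1.815 = 4.749 within districts.
- Five districts of six (3:3 in each): district cancels fully. SE = √(2 × 4.749 / 15) = 0.796.
- Ten districts of three (2:1 in five, 1:2 in five): each district keeps a weight of 2/15 − 1/15 = 1/15. SE = √(2 × 4.749 / 15 + 10 × 1.815 / 225) = √(0.633 + 0.081) = 0.845.

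**Standard error that the model reports.** Trials were simulated (40,000 replicates), with the mixed model represented by its balanced equivalent, a t-test on RHC means. At f = 50%:
- Five districts: mean reported SE 0.905 against a simulated true 0.794, a ratio of 1.14.
- Ten districts: 0.920 against 0.843, a ratio of 1.09.

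**One-sided error and power, without and with fixed district effects.**

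| Layout | f | Error without district | Power without | Power with | Change (points) |
|---|---|---|---|---|---|
| 5 × 6 | 0% | 5.0% | 83.5% | 83.2% | −0.3 |
| 5 × 6 | 25% | 4.0% | 85.5% | 87.8% | +2.3 |
| 5 × 6 | 50% | 3.2% | 87.8% | 92.2% | +4.4 |
| 5 × 6 | 75% | 2.3% | 89.8% | 96.0% | +6.2 |
| 10 × 3 | 0% | 5.1% | 83.3% | 78.7% | −4.6 |
| 10 × 3 | 25% | 4.2% | 84.5% | 83.5% | −1.0 |
| 10 × 3 | 50% | 3.5% | 85.9% | 88.8% | +2.9 |
| 10 × 3 | 75% | 2.9% | 87.2% | 93.6% | +6.4 |

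With district in the model, the one-sided error is 4.8 to 5.1% in every row.

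The losses in the ten-district layout have two sources. Nine district terms reduce the residual degrees of freedom from 28 to 19. The forced 2:1 splits also raise the variance of the within-district comparison: averaging ten districts gives (1 + 1/2) / 10 = 0.15 times the RHC-mean variance, against 2/15 = 0.133, a ratio of 1.125.

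**The case against.** The strongest reply is that the error is conservative. At these inputs the one-sided error does not materially exceed 5%, so a claim of non-inferiority is protected. Nor is adding district a certain gain: with ten districts of three RHCs and a low district share, fixed effects lose power. The standard errors above also leave out the planned adjustment for baseline SBP, which may absorb part of any stable district difference. The protocol gives no figure for the district share. All of this stands. It limits the size of the point, but the stated model still omits the randomisation strata.

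A reader might go further in four ways that the document does not support.

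- **That the GEE uses an uncorrected sandwich variance and so gives intervals that are too narrow.** Section 4.6 names no variance estimator or reference distribution for the GEE. The only sandwich estimator in the protocol belongs to the cost-effectiveness regression in section 4.5. Small-sample corrections and degrees of freedom are commonly left to the analysis plan, which is not at hand. The direction is not settled either. An uncorrected sandwich with a normal reference would give about 6.6 to 6.8% two-sided error at 30% prevalence if district had no effect. With half of the between-RHC variance at district level and district omitted, the same method gives 4.1 to 4.7%.
- **That vaccine doses received before enrolment are wrongly counted.** The outcome in section 4.3.5 is a cumulative status, so earlier doses belong in it. Baseline adjustment would improve precision without changing what is counted.
- **That leaving baseline out of the binary models makes them invalid.** It affects precision only, and mortality has no baseline value.
- **That each district must supply an even number of RHCs.** That would change the design, and the analysis can respect the strata without it.

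**Conclusion.** The point holds as a mismatch between the randomisation and the stated models, of minor to moderate weight. Omitting district does not bias the SBP estimate. If district explains part of the variation between RHCs, the interval is too wide. At an assumed 50% share it is about 9 to 14% too wide, with a one-sided error of about 3 to 4% against the nominal 5%.

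The consequence is a test that is too cautious, with less power than the design could give. The benefit of adding district depends on two facts that the protocol does not state: how many districts the 30 RHCs come from, and how much districts differ. What adding district secures in all the scenarios tried is a one-sided error close to its nominal level. A gain in power is likely only when district matters or the strata are reasonably large.

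**What to change.** Amend section 4.6 so that every outcome model includes the stratification factor. For SBP and the other continuous outcomes, the model would contain arm, district and the baseline value, with RHC as a random effect. District can enter as fixed effects or, if the strata turn out to be many and small, as a random effect, which could limit the loss seen with ten districts of three. The choice should be fixed before any unmasked data are seen.

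For the binary outcomes, state that district is included and add the baseline value of the same outcome where it is already collected: BP control status and COVID immunisation status. This is for precision. For rare outcomes such as mortality, name a fallback in case a district has no events, since a logit model cannot then estimate that district's term.

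The change is to wording only, with no new data. Its price is up to nine cluster-level degrees of freedom with fixed effects for ten districts, and the power changes tabulated above. State the number of districts once the RHCs are chosen, so that the form of adjustment can be settled on fact.
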